#### **7.4.2. Futility analysis**

A one-stage futility stopping will be based on conditional power (CP), the probability to detect a significant result at the end of the study, given the results observed at an intermediate time. This analysis is planned after a possible adaptation of sample size. CP will be estimated through B-values (85, 86).

This analysis will be carried out when at least 40% of the planned sample are available, and futility threshold will be  $CP_{min} = 0.10$  involving a slight increase of type 2 error ( $\beta = 0.1/0.9 = 0.111 - 0.10 \cong 0.01$ ) (87). None of these interim analyses require a type-I adjustment. Further details will be described in the Statistical Analysis Plan (SAP) as appropriate.

### **7.5. Individual patient Meta-analysis for a controlled result of efficacy**

#### **7.5.1. Principle**

This trial will assess the existence of an effect of AFMT on MB recovery, from MB deterioration caused by medication. However, no control group was provided. Thus it is not possible at this stage to separate the assumed MB recovery caused by AFMT from a natural evolution that should otherwise have been measured in a control placebo group. Another observational study [ULYSSE study] has been planned conjointly with the same patient selection and measurements. The observational study will then provide us with a control group through an individual patient data (IPD) meta-analysis.

|                                                                                                         |                      |                                                                                               |
|---------------------------------------------------------------------------------------------------------|----------------------|-----------------------------------------------------------------------------------------------|
| [figure not shown]
MaaT Pharma | Protocol             | Protocol N°: MPOH02
EudraCT N° : 2015-004335-12
Version 10.0
Date : 20 November 2017 |
|                                                                                                         | ODYSSEE STUDY |                                                                                               |

### **7.5.2. Inferential Aspects**

We plan to conduct an Individual Patient Meta-analysis (IPDM) aiming at assessing the AFMT effect compared with no treatment in recovering the initial MB previously deteriorated by medication.

The inferential model will be:

$$HR_i = k_0 + k_b.H_i + k_c.S_i + k_t.FMT + \eta.center \quad \text{where for } i=b,d,t \quad [4]$$

This model is similar to [1] except that a treatment effect (FMT) is coded 1 or 0, following that the patient has been administered AFMT (in this study) or not (in the observational study). As the decision to treat or not has not been randomized and originates from two separate studies, the comparison between baseline values of the two studies will identify variables  $X_i$  for which differences were identified on the two studies, and the used model will be adjusted for these variables as shown in the following model [5]

$$HR_i = k_0 + k_b.H_i + k_c.S_i + k_t.FMT + \eta.center + \sum w_i X_i \quad \text{where for } i=b,d,t \quad [5]$$

The above mentioned models [2] and [3] assessing the direction of the effect HS-S will be conducted by adding the main treatment (FMT) effect.

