## 7.3. Inferential aspects for criteria of efficacy

### 7.3.1. Co-primary endpoint: dysbiosis correction due to AFMT

The statistical distribution of Simpson index (S) will be fitted to a Normal or log-Normal distribution.

The significance of the AFMT effect will be assessed in assessing the significance of the differences  $\Delta = |S_f - S_d|$  by using a paired t-test.

In case where S is distributed as a log-normal distribution, the ratio  $S_f/S_d$  will be tested instead  $\Delta = S_f - S_d$ , by using a log transform. The transformation  $\text{Log}(S_f) - \text{Log}(S_d) = \text{Log}(S_f/S_d)$  allows to evaluate the difference of  $S_f$  and  $S_d$  in terms of ratio ( $S_f/S_d$ ).

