### **7.5.3. Secondary analysis : Generalization**

In the above model [5], H was elected within the set of HSR variables related with the patient health Status. There are several variables in this group called  $H_1, \dots, H_n$ . On the other hand, S was the Simpson index considered as the most usual measurement of the MB normality. However, this index is one among the multiple measurements of the MB, for which additional research is possible (cf section 7.2.2). By considering these possible variables  $S_1, \dots, S_m$ , the search of the effect of MB on Health, consists into the multivariate effect of the vector  $(S_1, \dots, S_m)$  on the vector  $(H_1, \dots, H_n)$ . This secondary analysis will be determined at the Statistical Analysis Plan level.

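### Section 7.5.2 aims at the AFMT effect on microbiota recovery, but its named models [4] and [5] have health status as outcome, adjust for same-time diversity, and code FMT as present before AFMT is given

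*Protocol*

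**What the plan says.** All references are to the protocol.

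- **Why a control is needed.** Section 7.5.1 says that, with this trial alone, "it is not possible at this stage to separate the assumed MB recovery caused by AFMT from a natural evolution". The ULYSSE patients are to supply the control group.
- **Aim.** Section 7.5.2 gives the purpose as "assessing the AFMT effect compared with no treatment in recovering the initial MB previously deteriorated by medication".
- **Model.** The inferential model named for that purpose is [4], which begins "HR_i = k_0 + k_b.H_i + k_c.S_i + k_t.FMT" and then adds a centre term. Model [5] adds covariates X_i. The index i runs over b, d and t in both.
- **Outcome.** HR is not defined. Section 7.5.2 states "This model is similar to [1] except that a treatment effect (FMT) is coded 1 or 0", and [1] in section 7.3.3 has health status H_i on the left. Section 7.5.3 confirms of model [5] that "H was elected within the set of HSR variables related with the patient health Status", while S is the Simpson index.
- **Treatment term.** "a treatment effect (FMT) is coded 1 or 0, following that the patient has been administered AFMT": the code follows study membership.
- **Covariates.** For X_i, "the comparison between baseline values of the two studies will identify variables" that differ between the studies.
- **Other controlled models.** Section 7.5.2 closes by adding the FMT term to [2] and [3] as well. These are described as assessing the direction of the relation between health and S. Model [3] has S_i as outcome, with S and H of the preceding time as regressors.
- **Single-arm test.** Section 7.3.1 says of the paired test of Sf against Sd: "The significance of the AFMT effect will be assessed in assessing the significance of the differences".

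**The concern.** The protocol concedes that the single arm cannot separate AFMT from natural recovery and turns to ULYSSE for a controlled answer. The equation given for that answer addresses a different question. Its outcome is health rather than the microbiota, and it holds constant the quantity that AFMT is meant to change. Its treatment indicator is also switched on before treatment. A small or null k_t could then be read as absence of an AFMT effect on diversity when the model was not able to show one. Meanwhile the uncontrolled paired test in 7.3.1 carries the label of AFMT effect.

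**Working it through.** The protocol states no figure for this analysis, so there is none to reproduce. The check is the algebra of the models, followed by a simulation.

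**1. Timing.** Section 6.4.2 puts the V2 sample within three days before antibiotics stop (about D29) and AFMT 24 hours after they stop (D30 and D31). V3 is about D40. Of the three times in section 7.3.3, baseline and deterioration both precede AFMT, and only the final value follows it.

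**2. What k_t measures in [4].** Take the final time, with H lagged as in [1], and let AFMT raise final diversity by tau:

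- S_f = m + tau·FMT + other terms
- H_f = k_0 + k_b·H_d + k_c·S_f + k_t·FMT

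Substituting, the total AFMT effect on health is k_c·tau + k_t. The effect on the microbiota is tau. The coefficient k_t is neither of these: it is only the part of the health effect that does not pass through S. This follows from the form of the model.

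**3. What the constant code does in [3] plus FMT.** Because [3] is lagged, the baseline row has no predecessor and drops out. Two intervals remain: b to d, where AFMT cannot act, and d to f, where it adds tau. One constant coefficient over two equally sized sets of rows gives roughly (0 + tau)/2 = tau/2.

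**4. Simulation.** Least squares, 1,500 replicates per scenario. Assumptions:

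- 20 AFMT patients, and 20 or 40 controls (the protocol does not give the size of ULYSSE)
- S as a ratio to baseline or on its absolute scale
- health depending on S with coefficient 1, and no direct AFMT effect
- [4] read with lagged H; rows d and f pooled for [4] and [3]
- centre and patient random effects left out

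Mean estimate of the FMT coefficient, as the range over the four combinations of control size and scale:

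| True tau | [4] | [3] + FMT, constant code | Sf on Sd, H_d, FMT | H_f on H_d, FMT, without S |
|---|---|---|---|---|
| 0.1 | -0.001 to 0.002 | 0.048 to 0.053 | 0.099 to 0.101 | 0.097 to 0.101 |
| 0.2 | -0.001 to 0.000 | 0.099 to 0.101 | 0.198 to 0.200 | 0.198 to 0.200 |
| 0.4 | -0.005 to 0.001 | 0.198 to 0.203 | 0.400 to 0.403 | 0.399 to 0.405 |

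The last column equals tau because k_c was set to 1, so the total health effect is 1 × tau.

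The constant code also costs precision. With 20 controls on the ratio scale and tau = 0.2, the mean divided by its standard deviation over replicates is 0.099/0.063 = 1.6 for [3] plus FMT, against 0.198/0.056 = 3.5 for the model of Sf.

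**5. The equation as printed.** Model [4] has H_i on the right at the same index as HR_i on the left, where [1] has H at i-1. If HR is H, the printed equation is solved by k_b = 1 with every other coefficient zero. The index t also stands where section 7.3.3 denotes the final value by f.

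**The case against.** **There is a controlled model with diversity as outcome.** This stands. A reader might infer that [4] and [5] are the only controlled analysis, so that the controlled answer is null by construction. The last sentence of 7.5.2 rules that out: [3] with FMT added has S_i on the left, and in the simulation it was diluted to about half, not to zero. It does not resolve the problem, because it is not the model named for the aim, it is presented as a test of direction, and its FMT code covers a pre-AFMT interval.

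**The analysis is exploratory.** This also stands. Section 7.5.4 says that study and treatment are confounded and that no treatment effect can be concluded. The primary analysis is the paired test, so a reader should not infer that the primary result depends on [4]. The admission does not mention the outcome, the adjustment for diversity or the timing of FMT, and these are avoidable.

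**k_t is not meaningless.** Correct. It is a direct-effect coefficient, and it is zero only if AFMT affects health solely through Simpson diversity. It is still not the effect that the aim names.

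**The index on H is a slip.** Probably so, given the stated similarity to [1]. It needs an editorial correction.

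**The limit of the single-arm test is disclosed.** Section 7.5.1 does disclose it. What remains is the label used in 7.3.1.

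**Comparability of the controls.** A reader might infer that ULYSSE patients escape the eligibility conditions that apply before AFMT. Section 7.5.1 states that patient selection is the same, and the ULYSSE protocol is not at hand, so the documents do not support that.

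**Conclusion.** The concern holds for the named models. The coefficient k_t in [4] and [5] does not estimate the AFMT effect on microbiota recovery that 7.5.2 sets as its aim. That conclusion rests on the written equations and visit timing alone. This is not detail left for a later plan, because the protocol writes out the equation.

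The sizes depend on the simulation assumptions. The mean of k_t near zero in [4] needs AFMT to act on health only through S. The factor of about one half for [3] plus FMT depends on pooling one pre-AFMT and one post-AFMT interval.

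Choosing X_i by observed baseline differences is a lesser weakness of the same section: in samples of this order, a confounder can matter without showing a clear difference. No figure is attached to it, because the ULYSSE size and the selection rule are not given.

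The point should be corrected before the combined analysis is run. It does not undermine the trial, since the comparison is exploratory and would remain so after correction.

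**What to change.** 1. **Microbiota aim (7.5.2).** Name one controlled model with one row per patient: Sf = k_0 + k_1·Sb + k_2·Sd + k_t·FMT + centre + covariates X, on the scale chosen under 7.3.1. With one post-AFMT outcome per patient, FMT acts only after AFMT. If Sf and Sd stay as ratios to baseline (7.1.1), enter Sb as the unscaled baseline value, since the ratio is 1 for everyone. Include centre only where it can be estimated alongside FMT.
2. **Covariates.** Fix X in advance instead of selecting it from observed baseline differences.
3. **Health outcomes.** If the total AFMT effect is wanted, model post-AFMT H on pre-AFMT H and FMT without post-AFMT S. A model that keeps S can be reported as a direct-effect analysis under that name.
4. **Notation.** Define HR, correct the index on H in [4] and [5], and use one symbol for the final time.
5. **Section 7.3.1.** Describe the paired test as the change from Sd to Sf (V2 to V3), in line with 7.5.1.

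The cost is a rewrite of 7.5.2, one sentence in 7.3.1 and slightly more analysis work, with no new data. The uncontrolled claim becomes weaker, and the comparison with ULYSSE stays exploratory because study and treatment remain confounded.

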### **7.2.2. Effect of dysbiosis correction on patient clinical status**

Previous researches provided some evidence of the association between the observed disorder or disturbance of the normal microbiota and the patient health status, infectious and digestive status. In the following, we call these variables Health Status Related HSR variables. In particular, one of them is the MDRB measured at each visit of the trial. For simplification of description of the following development, we keep the general term HSR to represent any health-status related variable measured, although the MDRB reduction will constitute the most important endpoint among any possible HSR.

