### 7.3.3. Secondary analyses : Association between S and health status

The assumed hypothesis is that the deterioration of the microbiota (MB) is associated with patient health status. In what follows, we consider one variable H in particular among the candidate HSR set, with  $H_b$ ,  $H_d$  and  $H_f$  designating the three values measured at baseline, deterioration and final times, respectively. Let us consider the following model:

$$H_i = k_0 + k_b.H_{i-1} + k_c.S_i + \eta_{i,\text{center}} \quad \text{for } i=b,d,t \quad [1]$$

|                                                                                                         |                      |                                                                                               |
|---------------------------------------------------------------------------------------------------------|----------------------|-----------------------------------------------------------------------------------------------|
| [figure not shown]
MaaT Pharma | Protocol             | Protocol N°: MPOH02
EudraCT N° : 2015-004335-12
Version 10.0
Date : 20 November 2017 |
|                                                                                                         | ODYSSEE STUDY |                                                                                               |

This model is a mixed model by considering the 3 measurements correlated within the patient random factor. The estimates are  $k_0$ ,  $k_b$ ,  $k_c$ , and the standard deviation  $\eta$ . This model assumes the instantaneous association between the MB diversity  $S$  and the health status, and tests the existence of an association between  $H$  and  $S$ , however, without possibility to test either relationship  $H \rightarrow S$  or  $S \rightarrow H$ .

However, this model can be tested in two different ways:

$$H_{i+1} = k_0 + k_b.H_i + k_c.S_i + \eta.\text{center} \quad \text{where for } i=b,d,t \quad [2]$$

In this model [2], health status (HS) at time  $(i+1)$  is assumed dependent on MB diversity at time  $i$ . This model will test the effect of MB diversity as a directional effect of lag=1 on HS, in other words, MB status affects HS with some delay, such result providing some evidence of a causal effect of MB on HS.

Another formulation should be

$$S_i = k_0 + k_b.S_{i-1} + k_c.H_{i-1} + \eta.\text{center} \quad \text{where for } i=b,d,t \quad [3]$$

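### Models [4] and [5] of the meta-analysis use an undefined response and put the health covariate at the same visit, so they are not model [1] plus treatment as the text says

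*Protocol*

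**What the plan says.** Protocol section 7.3.3 takes a single health variable for its models: "we consider one variable H in particular among the candidate HSR set". Model [1] relates that variable to its own previous value and to diversity at the current visit: "H_i = k_0 + k_b.H_{i-1} + k_c.S_i". Model [2] moves the response one visit ahead: "H_{i+1} = k_0 + k_b.H_i + k_c.S_i".

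Section 7.5.2 brings in the patients of the observational study as controls. Model [4] reads "HR_i = k_0 + k_b.H_i + k_c.S_i + k_t.FMT", plus a centre term. Model [5] is the same with baseline covariates added. The text then states how [4] relates to [1]: "This model is similar to [1] except that a treatment effect (FMT) is coded 1 or 0". It also says: "The above mentioned models [2] and [3] assessing the direction of the effect HS-S will be conducted by adding the main treatment (FMT) effect".

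Section 7.5.3 refers back to the health variable of [5] as H, not HR: "In the above model [5], H was elected within the set of HSR variables related with the patient health Status". The only collective label the protocol defines is HSR, in section 7.2.2: "we keep the general term HSR to represent any health-status related variable measured". The symbol `HR_i` is never defined.

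**The concern.** The equations for [4] and [5] and the sentence describing them cannot both be right. The sentence says that only the treatment term is new. In print, two other things have changed: the response symbol is now `HR`, and the health covariate has moved from the previous visit to the current one. The change appears in both equations, so it is not an isolated misprint.

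This matters because section 7.5.1 concedes that the single-arm trial cannot separate recovery due to AFMT from natural evolution, and relies on this meta-analysis for a control group. Models [4] and [5] are the only controlled models written out in full, and [5] is the only one printed with adjustment for baseline differences between the studies. As they stand, the analyst has to choose both the response and the conditioning variable, possibly after seeing data, and `k_t` depends on that choice.

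**Working it through.** The protocol gives no sample size, power or effect size for [4] and [5], so there is no figure to reproduce. The check is algebraic, with a simulation to illustrate it.

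**1. The equations side by side**

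| Model | Response | Health covariate | Diversity | Treatment |
|---|---|---|---|---|
| [1], 7.3.3 | `H_i` | `H_{i-1}` | `S_i` | none |
| [2], 7.3.3 | `H_{i+1}` | `H_i` | `S_i` | none (FMT added in 7.5.2) |
| [4] and [5], 7.5.2 | `HR_i` | `H_i` | `S_i` | FMT |

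**2. The possible readings of `HR_i`**

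- *`HR_i` is `H_i`.* This follows from the stated likeness to [1] and from section 7.5.3, which names only H. Least squares minimises the sum of (`H_i` − `k_0` − `k_b.H_i` − `k_c.S_i` − `k_t.FMT` − centre terms)². Setting `k_b` = 1 and every other coefficient to 0 makes each residual 0, and no smaller sum exists. If the columns are linearly independent, the solution is unique. Hence `k_t` = 0 whatever AFMT does. The covariates added in [5] also get weight 0. With zero residual variance there is no valid standard error or test.
- *`HR_i` is another health variable.* Then [4] is not [1] plus treatment. At the final visit the model also holds fixed a health variable measured after AFMT.
- *`HR_i` is `H_{i+1}`.* That is model [2] with FMT, which section 7.5.2 lists separately.

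No reading makes the printed equation agree with its description.

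**3. Simulation**

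Assumed inputs: 20 AFMT and 20 control patients, three visits, four centres as fixed effects, and a true AFMT effect on H at the final visit of 0, 1 or 2. There were 1000 runs per setting, fitted by least squares. Diversity S was generated independently of AFMT. Entries are the mean of `k_t`.

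| Model fitted | True 0 | True 1 | True 2 |
|---|---|---|---|
| `HR_i` = `H_i`, as printed, all visits | 0 | 0 | 0 |
| `H_{i-1}` on the right, final visit only | 0.01 | 1.00 | 1.98 |
| `H_{i-1}` on the right, both transitions pooled, FMT constant per patient | 0.00 | 0.50 | 1.00 |
| `HR_i` another variable correlated with H, all visits | 0.00 | 0.29 | 0.46 |

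In the first row the largest absolute `k_t` in any run was about 3e-15, `k_b` was 1.000 and the residual sum of squares was about 1e-28: the identity, up to rounding.

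The third row shows dilution. AFMT cannot act on the transition from baseline to deterioration, so pooling averages it with the later one: (0 + 1)/2 = 0.50 and (0 + 2)/2 = 1.00.

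The last row shows only that `k_t` is not zero under that reading. Its size mixes pooling over three visits with conditioning on H, and is not a measure of bias from either.

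**The case against.** A reader might infer that [4] and [5] as printed give an AFMT coefficient of exactly zero, that the trial would therefore report a false null, and that its whole controlled comparison is lost. The documents do not support this.

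- The printed response is `HR_i`, not `H_i`. The exact zero needs the inference that the two are the same. That inference is well supported, but it remains an inference; under another reading `k_t` is not zero.
- [4] and [5] are not the only models that use the control patients. Section 7.5.2 also adds the treatment term to [2] and [3]. Neither has its response among its own covariates, and [3] has diversity as its response, which is closest to the stated aim of recovering the initial microbiota.
- A variable regressed on itself leaves no residual. Any analyst would see this at once, so it would not be reported as an absent effect.
- The sentence likening [4] to [1] tells the analyst what was meant, and the protocol's notation is loose elsewhere: the visit index runs over b, d, t although the final time is called f. A slip in a symbol or subscript is the likeliest cause.
- Section 7.5.4 calls the analysis exploratory and says that no treatment effect can be concluded from it. No co-primary endpoint or sample size depends on it.

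All of this stands, and it lowers the severity. It does not make the equations right. This is also not detail left to a later plan: the protocol states a model, states it twice, and contradicts it in the next sentence.

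**Conclusion.** The point holds as an error in specification. The response in [4] and [5] is undefined, and the index of the health covariate contradicts model [1], which [4] is said to extend. If `HR_i` is `H_i`, the models are degenerate and `k_t` carries no information. If it is another health variable, they are a different model from the one described. In neither case do they provide the intended AFMT comparison. Models [2] and [3] with FMT added are not touched by this.

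Severity is low, for the reasons that stand above. The degeneracy is algebraic and needs no assumption beyond `HR_i` = `H_i`. The simulated values for the lagged model do rest on assumptions: the number of controls, the visit structure, and AFMT not acting through S. The point concerns the health term only and does not assess the use of `S_i` as a covariate.

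**What to change.** In [4] and [5], write `H_i` on the left and `H_{i-1}` on the right:

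`H_i = k_0 + k_b.H_{i-1} + k_c.S_i + k_t.FMT + ...`

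Delete the symbol `HR`. State that the model applies only to visits with a previous value, that is, deterioration and final but not baseline. Estimate `k_t` at the final visit, or code FMT as 1 only after AFMT has been given. If both transitions are pooled with FMT constant per patient, the coefficient is diluted (0.50 for a true 1.00 in the assumed simulation).

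The cost is a correction to two equations and one sentence on visits and coding, carried into the statistical analysis plan before the analysis starts. It needs no further data and no further patients.
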